## Abstract

We investigate the subjective experience of space around the visual blind spot area, the cortical representation of which is missing feedforward connectivity from one eye. We performed these experiments as part of an adversarial collaboration to test contrasting theories of consciousness; Integrated Information Theory (IIT), Predictive Processing Active Inference (AI), and Predictive Processing Neurorepresentationalism (NREP) accounts. According to the Integrated Information Theory of consciousness, non-activatable retinotopic cortical regions, such as the blind spot region for the ipsilateral eye, create a different cause-effect structure and therefore should contribute differently to the perceived quality of space of activatable retinotopic regions. The two Predictive Processing accounts, in contrast, posit that internal models will accommodate structural deviations around the blind spot based on the available sensory evidence (particulars of this accommodation differ between the two accounts). We present a series of paradigms in which participants evaluate distances and areas that either include the blind spot or not (without stimulating it directly), as well as illusory motion that is either adjacent to the blind spot or not. We model psychometric functions relating perceived and objective space. These models vary in terms of bias and precision according to the experimental conditions (blind spot involved vs. not involved, ipsilateral vs. contralateral eye), making it possible to quantify the potential disruption of subjective spatial extendedness induced by the blind spot. We present simulated results for each experiment corresponding to the predictions of each account and conclude by discussing challenges and plans for dissemination.

## Introduction

At the cortical level, the region of the primary visual area that represents the physiological blind spot has structural deviations that can be studied during monocular viewing. Compared to other regions of our visual field which rely on feedforward information from the lateral geniculate nucleus (LGN), the cortical representation of the blind spot exploits its lateral and feedback cortical connectivity for filling-in processes ([1–4]). For this study protocol, three theories of consciousness, integrated information theory (IIT, [5]), and, in the context of predictive processing, active inference (AI, [6,7]) and neurorepresentationalism (NREP, [8,9]) make different predictions about the behavioural effects that the blind spot’s structural features, relative to non-blind spot regions, may have on the conscious perception of space. We present very compressed descriptions of the three theories and their predictions that are sufficient to motivate our experimental procedures. Further details on the three theories and the derivation of these predictions are available here: https://osf.io/35rhx.

IIT posits that when spatial judgements involve the blind spot, the difference in connectivity (i.e., absence of feedforward input) in that region would contribute to a different cause-effect structure relative to the one of a comparably eccentric region. According to IIT, the quality of spatial consciousness is determined by the specific composition of a cause-effect structure. Thus, the theory proposes that the perception of space should be altered when involving the blind spot region. By contrast, both AI and NREP are based on the assumption that perception relies on internal models that are optimised to reduce prediction errors. In the case of the blind spot, internal models should adapt to accommodate for the blind spot’s structural deviations. Specifically, NREP posits that lesions of portions of the visual field can have an effect on spatial estimates, but will be largely compensated for by the sensory evidence available from intact portions of the visual field. According to AI, the quality of spatial experience is determined by the cause-effect structure under a generative model apt for active vision. This model of projective geometry is not the geometry of anatomical projections. Thus, AI proposes that perceptual judgements should not be altered when involving the blind spot, other than possible changes in perceptual uncertainty, due to differences in sensory sampling (e.g., decreases in psychometric sensitivity). As a result, both predictive processing-based accounts (AI and NREP) propose that perceptual distortions should be either absent or small when involving the blind spot. These predictions were derived as part of a larger multi-experiment structured adversarial collaboration.

### Integrated information theory

Integrated information theory (IIT) claims that the quality of a conscious state is given by a maximally irreducible structure of the causes and effects of a system (e.g., of a neural nature), namely, its cause-effect power ([10]). In the case of visual space, the theory predicts that the experience of space is defined by the cause-effect power of a grid-like substrate and, due to its grid-like networks, proposes the retinotopic cortex as a plausible candidate ([5]). If changes in connectivity between neurons in the grid-like network of the retinotopic cortex affect the cause-effect power of the mechanisms it composes, the quality of spatial consciousness would also change: the maximally irreducible cause-effect structure would differ between differently-connected versions of the network. When applied to the blind spot, differences in connectivity between monocular and binocular cortex may lead to differences in the visual space within versus outside the blind spot region. This could be measurable when comparing spatial percepts that span or do not span the blind spot insofar as lateral connectivity in V1, that makes V1 a grid-like network, differs from binocular to monocular cortex in this region. Since there is *less visual cortex* corresponding to the blind spot ([11]), IIT can be taken to predict that it may feel like there is *less visual space* in the blind spot region.

### Predictive processing (AI, NREP)

Set within the general Predictive Processing framework, both Active Inference (AI) and Neurorepresentationalism (NREP) accounts are based on the assumption that perception relies on internal models that are optimised to reduce prediction errors, therefore working against perceptual distortions.

With respect to consciousness, AI claims that shifts in conscious perception require active inference, which refers to planning and decision-making in terms of inference of policies for action (such as decisions to shift attention, or engage in eye movement), where policies are inferred under the expectation they will reduce uncertainty about the hidden states of sensation ([6,7,12–14]). Uncertainty reduction equates to belief updating, which can be inferred through participants’ behaviour as a proxy of conscious perception. With respect to the physiological blind spot, AI proposes that the internal models compensate for structural deviations, arguing against perceptual distortions being associated with the physiological blind spot. However, given that internal models have noisier sampling in and around the blind spot region, AI predicts that judgements involving the blind spot should be more variable (i.e., no difference in terms of accuracy but less precision).

By contrast, NREP proposes that conscious perception arises from the interplay between low-level and high-level sensory inference, where low-level refers to inferential processing in neural ensembles and small networks, whereas ‘high-level’ involves inferences between submodalities (e.g., color, shape) and main modalities (e.g., vision and touch; [9,15]). When applied to spatial consciousness, NREP posits that the experience of extendedness arises from the integration of different spatial frames of reference (e.g., retinotopic, craniotopic, allocentric; [8]), relying on inferences made jointly across visual field portions, proprioceptive signals from eye and head movements, vestibular changes, etc. This integrative processing not only takes place in lower visual cortical areas (e.g., V1), but also in higher associative areas, such as parietal and middle temporal cortex ([16,17], cf. [18]). With respect to the blind spot, NREP predicts that contextual information derived from cortical regions representing intact portions of the visual field should enable the subject to roughly create the same global predictions about the causes of sensory stimulation as those derived from undistorted connectivity maps. Following this, NREP predicts there will be no major spatial disruption if spatial inference mechanisms can sufficiently rely on the intact portions of the visual field (i.e., portions around the blind spot) to produce accurate spatial parameter predictions (e.g., on distance). However, since it is possible that neural mechanisms infer spatial parameters using the through-blind spot information as well as around-blind spot trajectories, a modest decrease in spatial bias may be observed (‘modest’ understood as reaching a modestly significant p-value according to classical frequentist statistics).

### Current study

We describe a set of experiments that were developed based on predictions made by the three theories of consciousness that are tested in this adversarial collaboration (AI, IIT, and NREP). Our experiments form one protocol paper, which will be published alongside three others from the same adversarial collaboration (see https://osf.io/35rhx for all preregistered designs). Perceptual distortions across the blind spot have been tested before ([19,20]). The hypothesis that was tested in these papers was whether the missing neuronal representation is ‘stitched together at the level of retina’ or ‘cortex’ which would lead to substantial perceptual shrinkage around the blind spot. [19,20]) concluded that the distortions they observed were not big enough to favour the hypotheses of retinal or cortical stitching of retinal representations, but, instead, favoured a compensatory mechanism hypothesis, with little, or no, spatial distortion. In contrast, our aim is to assess whether the existence of the cortical blind spot affects the conscious experience of spatial extendedness for stimulation that does not stimulate the boundaries of the blind spot. For this purpose, it is essential that our procedures avoid effects of perceptual filling in processes as much as possible.

We propose three experiments that rely on estimating distance (Experiment 1), area size (Experiment 2) and motion curvature (Experiment 3) at locations that are near to the blind spot area (>1 degree visual angle – DVA – away) or away from the blind spot area for either the ipsilateral or contralateral eye through dichoptic presentation. The comparison between stimulus locations, and stimulated eye will allow us to assess the effects of the non-stimulated blind spot region on our measurements. All experiments will include eye tracking to ensure that our data are not influenced by stimuli triggering the boundaries of the blind spot as represented by receptive fields in the visual cortex (see [21–23]).

## Materials and methods

### Aim

We will explore the different theoretical accounts using three tasks quantifying different types of spatial perception in relation to the blind spot in healthy humans. In the distance task, participants will judge the distance of pairs of dots that either span or do not span the blind spot. In the area size task, participants will judge the apparent size of circles that either surround or do not surround the blind spot. In the motion task, participants will judge the apparent curvature of motion paths that either neighbour or do not neighbour the blind spot. Each task will be performed in a standard trial-based format, allowing us to measure psychometric functions relating stimulus parameters to perceptual judgments. From these functions, we can extract measures of judgment bias and precision (i.e., slope). In all three tasks, we will achieve stimulation around the perceptual blind spot by presenting stimuli dichoptically (see below).

### Status and timeline

In the latter part of 2020, two TWCF workshops were hosted online by one of the coauthors, [name], resulting in, (1) the formation of the TWCF Intrepid consortium, (2) the selection and design of four experimental paradigms capable of arbitrating amongst hypotheses derived from IIT, NREP, and AI-C. Out of these paradigms, we present the experimental protocols for ‘Experiment 2a’ (see https://osf.io/35rhx for all preregistered designs). From this, the consortium initially proposed a successful pilot grant, testing the viability and feasibility of the experiments in arbitrating between theories. After a successful piloting phase, a full grant application was submitted that was successfully awarded following peer-review. In mid 2021 (before the full grant application was submitted), the experiment team at University of Glasgow convened a meeting agreeing with [name] from York University, Toronto and [name] from the University of Bradford, Bradford (UK) to form the replication lab. In late 2021, following the success of the TWCF pilot grant, the Glasgow Lab ran piloting for proof-of-principle for the eye-tracking and behavioural components of the three experimental tasks (pilot start = 03/11/2021, end 15/01/2024). This design was then pre-registered on OSF (https://osf.io/35rhx). Participants provided informed written consent for all pilot experiments. Currently, piloting and paradigm development have been completed for our three experimental tasks and data collection is underway. Recruitment has not been completed. We estimate completion of A) participant recruitment and B) data collection by the end of 2025. We also expect C) results by the end of 2025.

Based on this process, the experiments described herein form one of four protocols to be published, each describing experiments derived from predictions of the three theories being tested (AI-C, IIT, and NREP). Moving forward, consistent with the principles of co-design, all amendments to the experiment protocol following this publication will be addressed by agreement between the teams at both Glasgow and Toronto data collection sites, and the three Intrepid consortium theory leads ([name], [name] and [name]). Each amendment will be documented in experimental reports in OSF (https://osf.io/35rhx) identifying the specific change and rationale. A set of general analysis principles will be agreed upon prior to the commencement of the study. This process will be overseen by the Data Analysis and Replication Committee (DARC) of the Intrepid Consortium.

### Participants

We will conduct experiments in parallel at the School of Psychology and Neuroscience, University of Glasgow (Glasgow, Scotland) and at York University (Toronto, Canada). We will share programming scripts and methodology between sites.

In these experiments, we will test neurotypical subjects with normal or corrected to normal vision. We will only include participants with corrected to normal vision in cases where calibration works reliably (correction lenses sometimes reflect infra-red light, which can disturb eye tracking).

We will recruit participants through each site’s internal recruitment system. Participants give written consent. Participants in Glasgow will be reimbursed for their time at a rate of £7/h; participants in York will be reimbursed at a comparable rate in CA$20 or course credit. Each site’s human research ethics committees have granted ethical approval for this project (College of Science and Engineering Ethics Committee, University of Glasgow – Application Number: 300200313; Toronto – York University’s Human Participants Review Committee, Certificate e2019-194).

We will assess the presence of space distortions on perceived distance, area size and motion trajectories in areas neighbouring participants’ blind spot region. The use of small dot stimuli to study spatial vision near the blind spot has precedent (e.g., [20]). We hypothesise that effects might be small, so we will use a larger sample size (32 participants per experiment) than typical studies of perception across the blind spot (e.g., [3,20,24,25]).

### Apparatus

Stimuli will be composed of simple geometric shapes presented dichoptically to the ipsilateral eye (either across the blind spot or across a region neighbouring the blind spot) or to the contralateral eye (at the same locations). We will use PsychoPy ([26]) to code the protocols and to control the stimulation. Experimental scripts will be shared between the University of Glasgow and the replication lab at York University.

At the University of Glasgow, the experimental procedure will be run on a Windows11 computer with an Intel(R) CoreTM i7-12700 CPU processor, an NVIDIA GeForce RTX 3070 and a 27“ DELL at 1920x1080 and 120 Hz. Participants’ viewing distance will be fixed at 57 cm from the screen using a chin and forehead-rest. Experimental stimuli will be presented dichoptically to participants with the use of red/green coloured glasses (see Fig 1A). We will record participants’ eye movements using an Eyelink 1000 eye-tracker camera (SR Research; Ottawa, Ontario, Canada) placed in front of the participant, below the screen.

**Fig 1 pone.0340593.g001:**
[figure not shown]
Dichoptic stimulation and colour calibration: A. Illustration of a given trial in which dot stimuli are presented to the contralateral eye (the left eye in this example). Through the use of the coloured glasses, the green coloured stimuli are visible to the contralateral eye alone, which is red filtered. By contrast, the blind spot patch is presented to the ipsilateral eye alone, which is green filtered. The dichoptic stimuli are experienced by the participant as if they were presented to both eyes. The blind spot mask is not visible to the participant (because of the ipsilateral blind spot, assuming correct fixation). To facilitate fixation, fusion stimuli are presented above and below fixation cross to both eyes B. Illustration of the colour calibration paradigm, in which the participant is presented with six dots located radially above and below the fixation. The experimenter blocks each coloured lens at a time to adjust the luminance of red and green separately. The final values of red and green luminance are experienced dichoptically as dark colours while remaining invisible through the respective lens filter.

At York University, the experimental procedure will be run on a Linux computer with an Intel© Core™ i7-12700K, an NVIDIA GeForce RTX 3060 and a 27“ACER at 1920x1080 and 144 Hz. The gamma will be linearized by PsychoPy using a colour characterization of the screen. Participants’ position and glasses will be as above. We will record participants’ eye movements using a LiveTrack Lightning eye tracker, (Cambridge Research Systems, Rochester, UK) at 500 Hz that will be placed ~30 cm (adjusted to calibrate individual participants) in front of the participant, below the screen.

### Colour calibration

To ensure that each stimulus is experienced dichoptically, participants will first complete a colour calibration task while wearing the red/green glasses (Fig 1B). In the task, participants will be presented with six coloured circles located radially from fixation, above and below the horizontal meridian. All circles will be coloured using PsychoPy’s rgb colour space (P-RGB; see Peirce et al., 2022 for details). Above the horizontal meridian, the leftmost circle will start faint green (P-RGB: [−1,.5, −1]) and the rightmost circle will start faint red (P-RGB: [.5, −1, −1]). The central circle will flicker between green and red every 200ms to help control subjective equivalence between these colours for the participant. By contrast, below the horizontal meridian, the leftmost circle will start faint red (P-RGB: [.5, −1, −1]) and the rightmost circle will start faint green (P-RGB: [−1,.5, −1]). The central circle will flicker between green and red every 200ms. To render the circles invisible through each coloured lens, stimuli will be projected on a khaki-coloured background made out of a mix of red and green (P-RGB: [.5,.5, −1]). We will use this same-coloured background during the blind spot mapping and for the main tasks.

The experimenter will block one coloured filter at a time as they adjust the intensity of green (up arrow increases value of green, down arrow decreases value of green) or red (left arrow decreases value of red; right arrow increases value of red). The participant’s task will be to select colour values that are invisible monocularly through their respective lens (note that while fixating the dichoptic perception is of dark colours).

### Eye tracking

Before beginning each task, participants’ eye movements will be calibrated using either the five-point calibration procedure (centre, upper, lower, left, right) and 5-point validation procedure (centre, upper, lower, left, right) of Eyelink 1000 (SR Research), or an analogous method in the LiveTrack system. Eye tracking will be recorded throughout the tasks and will be used to validate participants’ fixation. Eye gaze position will be described as the average position of both eyes. Correct fixation will be described as eye gazes that are less than 2 DVA away from the fixation cross, allowing for 1 DVA inaccuracy from each eye-tracker and 1 DVA of people’s fixation inaccuracy.

In the main tasks, a trial will start after participants have fixated correctly for 200 ms (minimum pre-trial fixation window). In cases where the participant fails to fixate correctly for 3s (maximum pre-trial fixation window) an automatic recalibration will be triggered. During trials when the participant’s gaze leaves the permitted fixation window (i.e., 2 DVA from fixation, checked at every frame refresh), the trial will be automatically aborted. When this happens, the fixation cross will change from a “+” shape to an “#’ as feedback that a broken fixation was recorded. Participants will be instructed to press the up key whenever this happens to return to the pre-trial fixation. We will also be able to perform re-calibrations manually with a key press (‘r’) to ensure that the eye tracking parameters remain accurate, and as a break from the fixation task whenever participants express tiredness (e.g., difficulty in fusing the fixation cross).

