### Experiment 2: Area task

See Fig 4 for an illustration of a single trial of this task. For each trial, we will present participants with two circles, one foveally and one peripherally. The location of the foveal stimulus will be fixed around the fixation cross (“fixation” location) with some random jitter (−0.5 to 0.5 in steps of 0.05 DVA, with separate jitter applied to the x and y coordinates relative to the center of the stimulus). The peripheral stimulus will either surround the blind spot (“around blind spot” location) or be at an eccentrically comparable location (“above blind spot” location) with some random jitter (−0.5 to 0.5 in steps of 0.05 DVA, with separate jitter applied to both x and y coordinates relative to the center of the stimulus). Foveal and peripheral stimuli will differ in area. Participants’ task will be to adjust the area of the fixation stimulus to match that of the peripheral stimulus using their mouse. Participants will register the final size selection with a mouse click.

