**Fig 4 pone.0340593.g004:**
[figure not shown]
Area task: We illustrate two given trials over time (t) in which A. the foveal circle’s size starts smaller than the peripheral one and B. the foveal circle size starts larger than the peripheral one. Participants’ task is to adjust the foveal circle’s area to match the peripheral circle area. In all cases participants report their final size selection with a mouse click. The size of the fixation cross is randomised between trials to prevent local cues from biasing participants’ responses. Note that while we represent the stimuli in black and white here, the real task will involve coloured stimuli and will be performed with the coloured glasses as shown in Fig 1A. This will allow us to present the stimuli either to the contralateral eye or ipsilateral eye.

Peripheral circles will always be of fixed diameter, which will depend on each participant’s blind spot size and padding (peripheral diameter = participant’s blind spot size along longest dimension + 1.5 DVA of padding). The starting size of the foveal circle for a given trial will be randomly sampled from a distribution of smaller (5 values subtracted from the peripheral circle diameter in steps of peripheral circle diameter/10) and larger sizes (5 values added to the peripheral circle diameter in steps of peripheral circle diameter/10) with respect to the peripheral circle size. Fixation size will be adjusted by the participant by scrolling their mouse up (foveal circle diameter + peripheral circle diameter/10) or down (foveal circle diameter – peripheral circle diameter/10). Troxler’s fading occurs when an unchanging peripheral stimulus is experienced to disappear as a participant fixates centrally ([27,28]). To minimise this illusion, the peripheral circles will be dashed (12 dashes each spanning 15 degrees, and with a gap of 15 degrees between adjacent dashes) and will alternate between two orientations about its centre, by a polar angle of 15 deg, back and forth every 366ms.

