For each trial, the circle stimuli (foveal and peripheral) will be presented dichoptically either to the contralateral or the ipsilateral eye, while the fixation cross and fusion stimuli will be presented to both eyes. To prevent participants from relying on local features to complete the task, the size of the fixation cross will be randomised across trials (sizes = 0.5 to 2.25 DVA in steps of 0.25 DVA) and jitter will be applied to both circles and to the fusion stimuli (jitter = 0.025 to −0.025 DVA in steps of 0.005 DVA, applied individually to x and y stimulus coordinates per trial). Foveal circles will always be presented surrounding the fixation cross (centrally plus positional jitter), while peripheral circles will be presented at a location that either surrounds the blind spot or is above the blind spot. For the peripheral location that surrounds the blind spot, circle stimuli will be situated centrally to the mapped blind spot location (plus positional jitter). To get the above location which does not surround the blind spot, a polar angle representing half the height of the blind spot plus the radius of the peripheral circle plus 2 DVA rotation of padding is added vertically to the centre of the blind spot.

Participants will complete a total of 50 adjustments (10 different start sizes: 5 larger than periphery, 5 smaller than periphery; each start size will be repeated 5 times) per eye and location (200 total adjustments) for each hemifield without a time constraint for responses. A full session of this task lasts approximately one hour.

Using this data, we will model the distribution of perceptual equivalence across trials, which will be allowed to vary in terms of bias and precision according to the experimental conditions (around vs not around the blind spot, ipsilateral vs contralateral eye), making it possible to quantify potential disruption of area perception induced by the blind spot.

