The exact locations of the motion traces (adjacent to and above blind spot) as well as the distance between the traces’ dot positions will be determined for each hemifield of each participant given their mapped blind spot area. For the adjacent to blind spot location, the second and third dot positions are above and below a point that connects the fixation cross with the centre of the mapped blind spot location. This point, on which the second and third dot positions are centred, is displaced from the centre of the blind spot by the participants’ blind spot size (blind spot width/2), the maximum width of the curved stimulus and padding (minimum = 0.5 DVA). The separation between the dots will be fixed at 2 DVA for all participants. The first and fourth dot positions will be displaced from the second and third by the curvature of a given trial (i.e., all dots will fall on a circle with radius = 1/curvature). All dots (1, 2, 3, 4) will be equidistant to their neighbours at all trials (distance1–2 = distance2–3 = distance3–4). The same procedure is used for the location above the blind spot except that a polar angle representing half the height of the blind spot plus 1.7° rotation of padding is added to the blind spot location.

Motion traces will be shown dichoptically to the ipsilateral or contralateral eye either adjacent to or above blind spot location. For each of these combinations, we will define 2 staircases, one for which the angle curvature starts as curved towards fixation (i.e., curvature = 0.4 for the right hemifield or curvature = −0.4 for the left hemifield) and one for which the angle curvature starts as curved away from fixation (i.e., curvature = −0.4 for the right hemifield or curvature = 0.4 for the left hemifield). This yields a total of 8 staircases that will run interlaced to compose one run. Each staircase procedure ends when it has lasted for at least 30 trials and 10 reversals.

Using this data, we will model psychometric functions relating apparent motion curvatures to the proportion of times they are chosen as being curved away from fixation. These functions will be allowed to vary in terms of bias and precision according to the experimental conditions (adjacent to vs above blind spot, ipsilateral vs contralateral eye), making it possible to quantify potential disruption of apparent motion perception induced by the blind spot.

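### The stated clearance of more than 1 DVA from the blind spot is not met by the protocol's own geometry, chiefly in Experiment 2, and the 2 DVA gate on averaged gaze cannot protect the boundary

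*Protocol article*

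**What the plan says.** Under Current study, the protocol article places stimuli "at locations that are near to the blind spot area (>1 degree visual angle" away. It says that eye tracking in all experiments ensures the blind-spot boundary is not triggered, and it calls avoiding filling-in essential.

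The Eye tracking section sets the gate: "Correct fixation will be described as eye gazes that are less than 2 DVA away from the fixation cross". It builds the 2 DVA from two parts, 1 DVA for tracker error and 1 DVA for the participant's own fixation error. The gaze signal is defined so: "Eye gaze position will be described as the average position of both eyes". A trial is aborted when this signal leaves the window.

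The geometry is set task by task:

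- **Experiment 1 (distance):** padding of 2 DVA on each side of the blind spot, with a common jitter of up to ±1 DVA for both dots.
- **Experiment 2 (area):** the peripheral circle's diameter is "blind spot size along longest dimension + 1.5 DVA of padding". Its positional jitter is first given as running from −0.5 to "0.5 in steps of 0.05 DVA, with separate jitter applied to both x and y coordinates". Later in the same section it is ±0.025 DVA "in steps of 0.005 DVA, applied individually to x and y stimulus coordinates per trial".
- **Experiment 3 (motion):** the middle dots are displaced from the blind-spot centre by half its width, "the maximum width of the curved stimulus and padding (minimum = 0.5 DVA").

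Main experimental design adds a second safeguard. A patch fills the mapped blind spot in the ipsilateral eye's colour, and participants press the spacebar if it becomes visible or if part of a stimulus vanishes.

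**The concern.** The blind spot moves with the ipsilateral eye. If that eye can be off target by more than the stimulus clearance while the trial still counts, the stimulus can touch or enter the blind spot, which the design says it must avoid.

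Contact would not be spread evenly over conditions. It arises almost only when the ipsilateral eye is stimulated at the blind-spot location, and the contralateral eye and the control location serve as comparators for that cell. A circle that has lost part of its outline is probably harder to match, so the artefact could appear as lower ipsilateral precision at the blind spot. In Table 1, IIT and AI predict that result and NREP allows it. Support for a theory could then rest partly on fixation error.

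**Working it through.** **1. The gate.** 1 DVA tracker error + 1 DVA fixation error = 2 DVA, so the article's window reproduces.

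**2. Minimum clearance = padding per side − maximum jitter.**

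| Task | Before jitter | After maximum jitter |
|---|---|---|
| Experiment 1 | 4/2 = 2.0 DVA | 2.0 − 1.0 = 1.0 DVA |
| Experiment 2, jitter ±0.5 | 1.5/2 = 0.75 DVA | 0.75 − 0.5 = 0.25 DVA |
| Experiment 2, jitter ±0.025 | 0.75 DVA | 0.75 − 0.025 = 0.725 DVA |
| Experiment 3, minimum padding, curvature 0.4 towards the blind spot | 0.5 DVA | no jitter stated |

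The Experiment 2 values apply along the blind spot's longest dimension. They stay below 1 DVA under either jitter and even with none. Experiment 1 reaches exactly 1.0 DVA, and only at maximum jitter.

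**3. Experiment 3 at ordinary curvatures.** The offset includes the stimulus's maximum width, so 0.5 DVA is the gap at the extreme only. With curvature 0.4 the radius is 1/0.4 = 2.5 DVA. With 2 DVA spacing, the half-angle between neighbouring dots is arcsin(1/2.5) = 23.58°. The width is 2.5 × (cos 23.58° − cos 70.73°) = 1.47 DVA, centre to centre. At zero curvature the dot centres therefore lie at least 1.47 + 0.5 = 1.97 DVA from the edge.

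**4. Gate against clearance.** The 2 DVA window exceeds 0.75 DVA. On the kindest reading, 1 DVA of the window is tracker error and true fixation error is at most 1 DVA; that also exceeds 0.75. If tracker error adds to the recorded offset, true gaze could be 2 + 1 = 3 DVA off.

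**5. Averaging.** The ipsilateral eye's offset equals the binocular mean plus half the difference between the two eyes. Equal and opposite errors leave the mean at zero, so the gate does not see them.

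**6. How often contact could occur in Experiment 2.** The documents give no distribution of gaze error, so these are assumptions: isotropic normal ipsilateral error truncated at 2 DVA, an elliptical blind spot of about 4.5 × 5.5 to 6.5 × 8.5 DVA, no tracker error and no participant aborts. Simulated share of accepted gaze positions at which the circle meets the mapped blind spot:

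| Gaze SD per axis | Jitter ±0.5 | Jitter ±0.025 |
|---|---|---|
| 0.25 DVA | 5-7% | about 0.4% |
| 0.5 DVA | 25-30% | 17-20% |
| 1.0 DVA | 55-62% | 52-59% |

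At the area control location in the same eye, with ±0.5 jitter, the share is about 0.5% or less at these SDs, and 1.3% even if gaze is uniform over the window.

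**7. The other tasks.** Experiment 1 gives about 0%, 1% and 5-6% at the same three SDs. In Experiment 3, for curvatures up to 0.1, the share is 0% at every SD tried if the stimulus width includes the dot radius. If it does not, it is about 0.4% at SD 0.5 and 6-7% at SD 1.0.

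**The case against.** The strongest reply is the patch. It is shown to the ipsilateral eye throughout each run and mapped so that any movement reveals it. Its edge should therefore show before gaze error uses up the clearance, and it follows the right eye. The fusion stimuli also act against vergence error. This stands in part: the percentages above take no credit for aborts and overstate contact in trials finally analysed. But the safeguard depends on self-report during a demanding task. The patch was mapped under the same 2 DVA tolerance. Missing pieces of a dashed circle that alternates every 366 ms may go unnoticed.

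The percentages also depend on the assumed gaze SD. With steady fixation and the smaller jitter, contact nearly disappears; at SD 0.5 DVA or more, Experiment 2 is exposed under either jitter. In the other direction, the shares describe single gaze positions, and area trials have no time limit, so contact at some moment in a trial is more likely than the table shows.

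A reader might infer that all three tasks are seriously compromised. The documents do not support that. Experiment 1 has 2 DVA of nominal clearance, and Experiment 3's 0.5 DVA gap belongs only to the extreme curvature at which one staircase per cell starts. Nor is the exposed cell the only one that tests the theories: Table 1 also registers contralateral predictions, including an IIT decrease in bias.

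**Conclusion.** The concern holds, mainly for Experiment 2. The clearance of more than 1 DVA contradicts the circle's 0.75 DVA per side on any reading of the jitter. A 2 DVA window on averaged gaze cannot, by itself, ensure that the boundary is untouched. These two conclusions follow from the article's own figures.

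The frequency of contact does not. The 5-7%, 25-30% and 55-62% rest on assumed gaze SDs, assumed blind-spot sizes and the ±0.5 jitter, before participant aborts. That contact is concentrated in the ipsilateral blind-spot cell follows from the geometry. It can therefore mimic an eye-by-location effect, most plausibly on precision; nothing here shows that it would shift bias in a predicted direction. Exposure in Experiment 1 is about 0-6%. In Experiment 3 it is limited to extreme curvatures towards the blind spot at minimum padding.

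**What to change.** 1. Keep the online gate. Add a pre-specified analysis restricted to trials in which the ipsilateral eye's own recorded gaze stays within a radius of the fixation cross set by that experiment's stimulus clearance. Apply the same radius in all four eye-by-location cells and report exclusions per cell. Measure the offset from the cross; re-referencing to pre-trial gaze would hide offsets the gate has already accepted. State that the 1 DVA tracker inaccuracy limits how finely this analysis can resolve clearances of 0.25 to 0.75 DVA.
2. Under Current study, replace the single clearance figure with each experiment's actual minimum, and drop the claim that eye tracking alone ensures the boundary is not triggered.
3. Reconcile the two Experiment 2 jitter values, and say which one the running script uses.

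Do not change the padding now. Data collection is underway, and in Experiment 2 the padding sets the diameter of the judged circle, so a change would split the sample between two stimulus sets.

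The cost is analysis code on gaze data that are recorded anyway, plus text corrections. The restricted analysis will lose some trials, mainly in Experiment 2.
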